## Background {6}

A common complication after cranial surgery is cerebrospinal fluid (CSF) leakage. Our recently published systematic review, summarizing data from 113 studies, showed an average postoperative CSF leakage rate of 2.9% in supratentorial procedures, 5.8% in infratentorial procedures, and 4.1% in endoscopic transsphenoidal surgeries. Postoperative leaks may require revision surgeries and/or external CSF drainage [2]. Adequate dural closure is necessary to prevent CSF-related complications such as infection and intracranial hypotension. Currently, commercially available fibrin sealants are considered the gold standard for dural closure, due to their hemostatic, adhesive, and sealant properties. However, problems regarding efficacy, cost, and safety have been reported.

A possible alternative to commercially available fibrin sealants is autologous fibrin rich in platelets and leukocytes. The technique to produce such fibrin membranes was first described by Choukroun et al. in 2001 [3]. Leukocyte- and platelet-rich fibrin (L-PRF) is currently applied as an autologous biomaterial in various specialties, including oral and maxillofacial surgery and sports medicine [4]. The main advantage of L-PRF is that it is completely autologous, thereby minimizing the risk of immunological reactions. L-PRF is readily available as it is derived from the patient’s own blood, and accordingly, the method for preparation is non-invasive. Finally, L-PRF can be prepared “bedside” during surgical procedures by the operating room staff, within a 20-min time frame. For L-PRF membrane preparation, blood is collected in glass-coated tubes and centrifuged at 400* g* for 12 min (Fig. 1). During centrifugation, platelets are activated and the coagulation cascade is initiated. This results in a fibrin clot, which can be compressed into a membrane, for use as an onlay graft or cylinder to plug defects. These flaps can be placed on a defect, where the leukocytes and platelets that are incorporated in the fibrin network deliver growth factors to the surrounding tissue. Analogously, liquid L-PRF glue can be prepared in plastic-coated tubes. Because of the hydrophobic surface and shorter centrifugation time (3 min), the product maintains its native fibrinogen and only coagulates in contact with other tissues [5].

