## Outcomes {12}

The primary endpoint is the success rate of both techniques, which means the absence of a clinically relevant CSF leak at 12 weeks after surgery, i.e., any leak that needs surgical revision or any other intervention, e.g., puncture or aspiration, longer hospitalization, or repeat imaging. The success rate in both groups will be reported in proportions with a 95% confidence interval.

Secondary endpoints include an analysis of peri- and postoperative complications (CSF leakage, both clinically relevant (incisional leakage) and not clinically relevant (swelling, pseudomeningocele), surgical site infection and treatment-site bleeding in particular), as well as a cost-effectiveness evaluation. In addition, the study will compare the efficiency of L-PRF in supratentorial and infratentorial surgery, based on surgical approach and technique.

Peri- and postoperative complications will be obtained from the hospital databases. Each complication requiring additional treatment (surgical revision, intervention, or drug therapy) or investigation (clinical or imaging) or which requires or prolongs hospitalization will be considered. RAND SF-36 questionnaires will be filled out preoperatively (baseline) and 6–12 weeks post-surgery to evaluate patient-reported health concepts such as physical functioning, bodily pain, role limitations due to physical health problems, role limitations due to personal or emotional problems, emotional well-being, social functioning, energy/fatigue, and general health perceptions. The questionnaire is scored as indicated on the official website of RAND, adapted from the scoring described by Ware and Sherbourne [10]. The difference in the change in score to baseline will be compared between the groups, i.e., treated with commercially available fibrin sealants or treated with L-PRF.

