### Sample size {14}

Sample size calculation was performed according to the primary outcome, using an online power calculator for binary outcome non-inferiority trials (Sealed Envelope Ltd. available from: www.sealedenvelope.com). This is a non-inferiority trial with a binary outcome using a one-sided alpha of 0.05 and 80% power. The assumed success rate is 93.7% in the control arm, based on center-specific experience as well as the literature [13]. Data on the use of L-PRF for this indication is limited, but we assume a 95% success rate based on a prior feasibility study [9].

The statistical hypothesis for testing the treatment difference is presented as follows: H_0_: Δ ≤  − 0.05 tested against the alternative hypothesis and H_A_: Δ >  − 0.05, where Δ is the difference between the success rates of experimental and control condition and − 0.05 is the non-inferiority difference. The non-inferiority limit was set at 0.05 considering (1) reported CSF leakage rates without commercially available fibrin sealant averaging 17.2% [14] and (2) important additional benefits of L-PRF compared to commercially available fibrin sealants including the completely autologous nature (eliminating immune reactions), presence of immunologic cells and reduced costs.

Based on this power calculation, 334 patients need to be included, 167 in each group. A drop-out rate of 2–5% is expected due to loss of follow-up and non-adherence to the allocation or failure of L-PRF preparation. Therefore, 350 patients will be enrolled, 175 in each group.

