### Assignment of interventions: allocation

#### Sequence generation {16a}—concealment mechanism {16b}—implementation {16c}

Patients are randomized into two groups, i.e., one arm treated with commercially available fibrin sealants and the other arm treated with L-PRF. The randomization sequence is generated by the study coordinator using an online randomization tool (www.sealedenvelope.com), for simple randomization with two treatment groups of equal size, no blocks, and no stratification factors. The allocation list is then uploaded into the Research Data Capturing solution (RedCap), a system where access is restricted to the study personnel. Only one subject’s allocation can be released at a time, after confirming that the patient is suitable for randomization. Participants are enrolled by the study coordinator or his/her delegate. Randomization is done during surgery using the Randomize-tool in RedCap by trained study personnel, other than operating room staff, for example, the study coordinator. The arm to which the patient is allocated is communicated by telephone to the operation theater staff.

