### Statistical methods

### Statistical methods for primary and secondary outcomes {20a}

Data will be analyzed in the GraphPad Prism software using a simple *t* test, or non-parametric Mann–Whitney *U* test when not normally distributed, with Bonferroni Holm correction for multiple testing. A *p*-value ˂ 0.05 is considered statistically significant. The primary outcome, i.e., CSF leakage, will be analyzed in terms of a difference in risk between the two treatment groups. The mean difference between the two treatment groups will be reported as a two-sided 95% confidence interval. Secondary endpoints will be calculated using a simple *t* test, non-parametric Mann–Whitney *U* test when not normally distributed, Fisher’s exact test, or chi-squared test, based on the number of events.

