### Methods for additional analyses (e.g., subgroup analyses) {20b}

Subgroup analyses will be performed for surgical indication (tumor, vascular or functional), craniotomy diameter (small: ˂ 30 mm; medium: ˃ 30 mm; ˂ 80 mm; and large: ˃ 80 mm) recurrent surgery, patient age, gender, medication use, and alcohol and smoking habits. The data will be statistically tested using a simple *t* test or Mann–Whitney *U* test, or Fisher’s exact test or chi-squared test depending on normality, type of variable, and number of events. We do not intend to perform adjusted analyses.

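### The plan rules out any adjusted analysis, although surgical location is known before randomisation, recorded and strongly prognostic; a location-stratified risk difference would be a small, nearly free improvement

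*Protocol article*

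**What the plan says.** Allocation: the sequence-generation section ({16a–c}) describes a list made "for simple randomization with two treatment groups of equal size, no blocks, and no stratification factors".

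Primary analysis: section {20a} says that CSF leakage "will be analyzed in terms of a difference in risk between the two treatment groups", with a two-sided 95% confidence interval. No covariate is named.

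Adjustment: section {20b} closes with "We do not intend to perform adjusted analyses". This is a stated decision, so an analysis plan that followed it could not add a stratified estimate.

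Location as a risk factor: Background {6} reports from the team's own systematic review an "average postoperative CSF leakage rate of 2.9% in supratentorial procedures, 5.8% in infratentorial procedures".

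Location as a question: Outcomes {12} adds that "the study will compare the efficiency of L-PRF in supratentorial and infratentorial surgery".

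Availability: location is part of the inclusion criteria in the study-setting section, randomisation takes place during surgery, and Outcomes lists surgical approach among the categorical variables to be reported.

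**The concern.** The protocol itself supplies the evidence that location predicts the primary outcome, with a ratio of 5.8/2.9 = 2.0. It then uses location neither in allocation nor in the primary comparison. If one arm happened to receive more infratentorial cases, its observed leak rate would tend to be higher for that reason alone. The shift would carry into the risk difference that is compared with the 5-point margin.

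Two things are at stake. One is a little precision. The other is an avoidable argument at the reporting stage. If the baseline table shows an imbalance by location, readers will ask for an adjusted estimate. Under the present wording, any such estimate would be post hoc and contrary to the protocol.

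**Working it through.** **Inputs from the protocol.** 350 enrolled, 1:1; control success 93.7% (leak 6.3%); L-PRF success 95% (leak 5%); margin 5 points; one-sided alpha 0.05; power 80%; review leak rates 2.9% and 5.8%.

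**Assumption.** The infratentorial share q is not given. I take 20–50%.

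**1. The plan's own sample size.** With unpooled variance, n per arm = (0.937×0.063 + 0.95×0.05) × (1.645 + 0.842)² / (0.013 + 0.05)² = 165.9. That is 166 per arm or 332 in total, against 334 stated, so the planning figures are reproduced.

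**2. Standard error of the risk difference with 175 per arm.** √[(0.0590 + 0.0475)/175] = 0.0247, or about 2.5 points.

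**3. Chance imbalance in location.** The SD of the between-arm difference in infratentorial share is √[4q(1−q)/350].

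| q | SD of imbalance (points) | 95% limit (points) |
|---|---|---|
| 20% | 4.3 | ±8.4 |
| 30% | 4.9 | ±9.6 |
| 50% | 5.3 | ±10.5 |

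**4. Resulting shift in the risk difference.** This is the imbalance multiplied by the risk gap between locations. At the review's rates the gap is 2.9 points. Scaled to a 6.3% overall control leak rate at the same 2:1 ratio, the gap is 6.3/(1+q) points: 5.25, 4.85 and 4.20 for the three shares.

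| q | Review rates: SD | Review rates: 95% limit | Scaled: SD | Scaled: 95% limit |
|---|---|---|---|---|
| 20% | 0.12 | ±0.24 | 0.22 | ±0.44 |
| 30% | 0.14 | ±0.28 | 0.24 | ±0.47 |
| 50% | 0.16 | ±0.30 | 0.22 | ±0.44 |

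Against the margin, 0.30/5 = 6% and 0.47/5 = 9%. In patients, 0.0047 × 175 = 0.8, so less than one event in an arm. At the review's gap, a shift of 1 point would need an imbalance of 1/2.9, or 34 percentage points.

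**5. Share of the variance.** In the least favourable scaled case, (0.24/2.47)² is about 0.9%. At the review's rates it is about 0.4–0.5% of the variance that those rates imply.

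**6. Simulation.** 20,000 trials per setting, 350 patients, simple randomisation, scaled rates, q = 20%, 30% and 50%, comparing the unadjusted risk difference with the Mantel-Haenszel one at one-sided 0.05.

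| Quantity | Unadjusted | Location-stratified |
|---|---|---|
| Power at the planned rates | 81.6–82.7% | 82.1–83.0% |
| Type I error at the margin | 5.4–5.8% | 5.5–5.7% |

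Stratifying lowers the variance by about 0.5–1% at the planned rates. I repeated the simulation with a different random seed. The power gain was again 0.4–0.5 points, and the two analyses reached a different non-inferiority decision in about 2% of trials. At one-sided 0.025 the power gain also stayed under 1 point.

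Step 4 holds the risk gap at its true value. In a single trial the observed gap is itself noisy, so the two estimates can lie somewhat further apart: in 95% of simulated trials they were within about 0.6 points of each other.

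**The case against.** The strongest reply is that nothing here is wrong. Simple randomisation with an unadjusted risk difference is valid and unbiased, and the confidence interval already allows for chance imbalance in every prognostic factor, location included. That stands in full. A reader might infer from the absence of strata and of adjustment that the primary comparison is compromised, or that an imbalance would bias it. The documents do not support that inference, and step 6 shows an essentially unchanged type I error and a negligible gain in power.

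Three further objections have force:

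- The twofold ratio comes from review averages for postoperative leakage. The primary endpoint is the narrower clinically relevant leak, and the protocol does not show that the ratio carries over to it at this centre. The infratentorial share is also unknown. The sizes above are therefore conditional, although they stay small across the range.
- A reader might suppose that a stratified estimate also answers the planned comparison by location. It does not. A pooled Mantel-Haenszel difference averages over location, whereas Outcomes {12} asks about L-PRF in one location against the other. That needs separate estimates by location.
- Events are few. About 175 × 0.063 = 11 are expected in the control arm and 175 × 0.05 = 9 in the L-PRF arm. At q = 20% the infratentorial stratum has some 35 patients and 3–4 events per arm. With one two-level factor the stratified methods still behaved well in the simulation, but this is a reason to stop at one factor.

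The objection shows that the gain is minor. It does not show a real cost in using a baseline variable that is already collected, or a reason to exclude every adjusted analysis in advance.

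**Conclusion.** The point holds as a small improvement to the analysis. It is not a defect in the allocation or in the primary comparison. The protocol closes off an adjustment for a factor that its own review marks as prognostic and that is available for every patient.

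For an infratentorial share of 20–50% and a 2:1 risk ratio, both assumed to apply to the primary endpoint, the shift from imbalance stays within about 0.3 points (review rates) to 0.47 points (scaled to 6.3%) at the 95% limit. That compares with a 5-point margin and a standard error of about 2.5 points. The return is a variance lower by about 0.5–1% and less than 1 point of power. The more practical benefit is that an adjusted estimate would be prespecified if the baseline table shows an imbalance.

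**What to change.** In section {20b}, replace the sentence that excludes adjusted analyses with a prespecified risk difference stratified by supratentorial or infratentorial location, using Mantel-Haenszel weights or the stratified Miettinen-Nurminen method. Report it with its confidence interval beside the unadjusted difference, and state in advance which of the two decides non-inferiority. Fix the wording before allocation is released; the blinding section {17} keeps allocation masked until the analysis is done, so this can still be settled blind.

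Leave the allocation list as it is, since recruitment has run since January 2020. Keep the comparison by location in Outcomes {12} as its own analysis, with estimates for each location.

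The cost is an amendment to the analysis wording and software that offers a stratified risk difference. No new data are needed.

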### Assessment of interventions: blinding

#### Who will be blinded? {17}

The randomization is single-blinded, i.e., enrolled patients do not know which group they are allocated to. Blinding of surgical staff is not possible as L-PRF is clearly different from fibrin sealants. The bias of surgeons is reduced as much as possible by announcing the treatment arm only after the dural opening. Paramedics at the neurosurgery hospitalization department do not have access to the randomization code, thus reporting bias is reduced during hospital follow-up. Researcher’s bias is reduced by reblinding subject allocation after surgery. For analysis, group allocation will only be released after the statistical analysis has been performed.

#### Procedure for unblinding if needed {17b}

Unblinding may be done after completion of the outpatient follow-up visit (FU3) or in case of any serious adverse event that is probably related to the study.

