**Methods/design:**

This single-blinded, prospective randomized controlled interventional trial aims to demonstrate the non-inferiority of L-PRF compared to commercially available fibrin sealants for dural closure. This trial will include patients undergoing cranial neurosurgery (supratentorial and infratentorial) with intentional opening of the dura. Patients are randomized in a 1:1 fashion comparing L-PRF to commercially available fibrin sealants. The primary endpoint is postoperative CSF leakage within 12 weeks after surgery. Secondary endpoints are complications such as bleeding or wound infections. Additionally, a cost-effectiveness analysis is performed.

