**Fig. 2 Fig2:**
[figure not shown]
Flowchart of “L-PRF in cranial surgery, a prospective randomized controlled trial.” After obtaining informed consent, patients are screened and asked to complete quality of life (QoL) questionnaires (EQ-5D and RAND SF-36). During surgery (i.e., before dural closure), study subjects are randomized into the experimental arm (L-PRF) and the control arm (commercially available fibrin sealants). During hospitalization, patients are followed up with clinical controls after 2 days (FU1) and on the day of discharge (FU2). One outpatient follow-up is done between 6 and 12 weeks postop (FU3), with MRI imaging and completion of the QoL questionnaires

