### Interim analyses {21b}

Per protocol, no interim analyses will be performed.

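### Completion of FU3, possible from week 6, is enough on its own to permit unblinding, although the primary endpoint runs to week 12

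*Protocol article*

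**What the plan says.** Section {17b} of the protocol article gives two separate routes to unblinding. The first is "Unblinding may be done after completion of the outpatient follow-up visit (FU3". The second, joined by an or, is "or in case of any serious adverse event that is probably related to the study". The first route names no reason, requester or recipient.

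The timing of FU3 is given in the caption of Fig. 2: "One outpatient follow-up is done between 6 and 12 weeks postop (FU3". The notes to Table 2 and the section on outpatient follow-up give the same window.

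The primary endpoint in {12} is "the absence of a clinically relevant CSF leak at 12 weeks after surgery"; the abstract says "The primary endpoint is postoperative CSF leakage within 12 weeks after surgery". Under {12}, a leak is clinically relevant if it leads to surgical revision or another intervention, and the examples include puncture, a longer stay and repeat imaging.

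Section {17} describes the blinding. Patients do not know their arm, surgical staff cannot be blinded, and researchers are reblinded to allocation after surgery. It closes with "For analysis, group allocation will only be released after the statistical analysis has been performed".

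**The concern.** The time at which blinding may end is tied to a visit that can take place halfway through the primary endpoint window. After that visit a patient is still at risk of a primary event, but the protection that {17} claims may already have been lifted.

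This matters because of how the endpoint is built. Whether a late leak counts depends on whether the patient returns, whether imaging is repeated, and whether a puncture or a longer stay follows. Knowledge of the arm can influence each of these. Surgeons are unblinded throughout, so patient blinding and researcher reblinding are the main safeguards left after discharge.

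Few events decide the result. At the protocol's assumed success rates of 93.7% and 95%, about 20 leaks are expected among 350 patients (175 × 0.063 + 175 × 0.05 = 11.0 + 8.8 = 19.8). The margin of 0.05 corresponds to about 8 patients in an arm of 167 (0.05 × 167 = 8.35). A small number of differently handled events could move the estimate. The document does not show in which direction.

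**Working it through.** The plan states no figure on this point. The sample size is not in dispute and is unaffected: recalculation from the stated inputs gives 166 per arm against the stated 167. The check is a comparison of sections, with simple arithmetic for the exposure.

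**1. Is FU3 enough on its own?** Yes. In {17b} the FU3 route and the serious-adverse-event route are alternatives, and only the second carries a condition.

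**2. How early can FU3 be complete?** Week 6 (Fig. 2 caption, Table 2 notes, outpatient follow-up section).

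**3. When does the endpoint window close?** Week 12 ({12} and abstract).

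**4. Exposed time per patient = 12 − week of FU3.**

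| FU3 at week | Endpoint weeks left | Share of the 12 weeks |
|---|---|---|
| 6 | 6 | 50% |
| 9 | 3 | 25% |
| 12 | 0 | 0% |

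If FU3 dates were spread evenly over weeks 6 to 12, which is an assumption, the mean would be 3 weeks. These are shares of calendar time, not of leaks. The document does not say when leaks occur, so the figures cannot be turned into a number of affected events.

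**5. Does another section close the gap?** No. Nothing makes post-FU3 unblinding wait for week 12, the end of recruitment or database lock. The last sentence of {17} governs release for the analysis. It does not say whether an individual patient or researcher may learn the allocation earlier under {17b}.

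**6. Could leak counts by arm build up during recruitment?** Assume even accrual of 350 patients over four years (three planned plus one added in {15}).
- Accrual: 350 / 208 weeks = 1.68 per week.
- Randomised by week 104: 175.
- Not yet past FU3: between 1.68 × 6 = 10 and 1.68 × 12 = 20.
- Past FU3: 155 to 165. At the pooled assumed leak rate of 5.65%, about 9 leaks are expected among them.
- Already past week 12: 175 − 20 = 155.

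Nearly all patients open to unblinding at that time would therefore have a closed endpoint window, so the figure of 9 does not measure biased classification.

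**The case against.** Several stronger readings are tempting. The document does not support them.

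- **That {17} and {17b} flatly contradict each other.** The closing sentence of {17} begins with the words for analysis. It can be read as governing the analysis dataset, with {17b} governing individual unblinding. The two sit uneasily together and need reconciling, but both can hold.
- **That unblinding at FU3 is routine.** The heading of {17b} says if needed and the sentence says may. It remains true that the FU3 route states no need. Who is told may be settled in the full protocol, which is not shown; whoever it is, the stated timing allows it inside the endpoint window.
- **That the clause creates a hidden interim look.** Section {21b} states "Per protocol, no interim analyses will be performed", and a reader might infer that {17b} defeats this. But the coordinator already generates the sequence ({16a}) and prepares the L-PRF ({11a}), so a tally by arm is possible from surgery onward with or without the clause. Nor does the document say that those who classify leaks are those who manage protocol changes.
- **That analysis before release of allocation cannot be done.** A directional comparison can be run on coded groups. Only analyses that need the product identity, such as as-treated and costs, require the labels.

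The strongest remaining objection is that FU3 is the last scheduled leak assessment, so unblinding follows the last planned ascertainment. That limits the exposure but does not remove it. A leak after FU3 and before week 12 is still a primary event, and it would come to light through an unscheduled contact, where the patient's and researchers' knowledge of the arm may matter. Two other safeguards in {17} are untouched: the arm is announced only after the dura is opened, and ward staff have no access to the code.

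**Conclusion.** The point holds in a limited form. As written, {17b} allows patient blinding and researcher reblinding to lapse with up to 6 of the 12 primary endpoint weeks still to run, and no other section prevents it. The affected events are leaks arising between a patient's FU3 and week 12. Their number cannot be estimated, because the document gives neither leak timing nor the distribution of FU3 dates. Part of the knowledge of allocation exists regardless, among surgical staff and the coordinator.

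This is an avoidable risk of bias in a partly judgement-based endpoint with few events. It is not evidence that bias will occur, and no stated figure changes. The conclusion rests on reading {17b} as it stands, with FU3 completion as the only condition of its first route. It is worth correcting because the change is small and, according to the trial status section, recruitment was still open at publication.

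**What to change.** In {17b}, replace the FU3 trigger with release of allocation only after the 12-week primary outcome has been recorded and the database locked. Leave the serious-adverse-event trigger exactly as written.

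Align the last sentence of {17} with this order:
1. Outcome classification and membership of the analysis sets are fixed without access to allocation, as far as the definition of each set allows.
2. The primary comparison is run on coded groups.
3. Labels are then released for the analyses that need the product identity (as-treated, costs).

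The cost is two sentences in an amendment. Sample size, visits and treatment do not change. The one practical drawback is that patients who ask which product they received must wait until database lock.

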### Data collection and management

#### Plans for assessment and collection of outcomes {18a}

Preoperative data is collected from the preoperative assessment of the anesthesiologist (medical history, comorbidity, and medication use) and neurosurgeon (surgical indication) available in the electronic patient files. Preoperative patient questionnaires are on paper source documents. Intraoperative data and used materials are collected from the neurosurgical report. Postoperative data during hospitalization is collected from hospitalization reports in the electronic patient files. Data from the outpatient follow-up are available in the electronic files. Postoperative questionnaires are filled out on paper source documents or electronically via RedCap. Data transfer from source documents to the RedCap data collection tool will be done by trained study personnel (research assistant). Regular data quality checks are performed in RedCap to ensure complete and accurate data transfer. Paper source documents will be stored for 10 years after completion of the study in a secure location at the study site.

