#### Adverse events reporting and harms {22}

Harms and adverse events that may be expected in the study population include intracranial hemorrhage, tension pneumocephalus, wound problems, and neurologic complications such as seizures, dysphasia, or motor deficits [15]. During hospitalization, harms will be systematically collected from documentation of clinical and radiological examinations and daily nursing reports in the electronic patient files. At the outpatient follow-up (FU3), harms will be collected based on anamnesis and clinical examination. Additionally, four open-ended questions will be presented to the subjects:

Did you suffer from any complaints?Have you been ill?Have you taken any medication?Were there any problems regarding wound healing?

During the study, all adverse events are recorded and notified to the sponsor with a yearly progress report. According to the local law, serious adverse events are reported immediately, after first knowledge, to the sponsor, accompanied by detailed written reports. A serious adverse event is defined as any untoward medical occurrence or effect that results in death, is life-threatening, requires hospitalization or prolongation of existing hospitalization, results in persistent or significant disability or incapacity, or is a congenital anomaly or birth defect. Serious adverse events defined as such will be reported in the final manuscript of the study. The sponsor shall keep detailed reports of all adverse events which are reported. For the reported death of a subject, the investigator shall supply the institutional Ethical Committee with any additional information requested.

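### The primary endpoint depends partly on discretionary decisions open to staff who know the arm, and some endpoint leaks may be unblinded before FU3 without first being classified

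*Protocol article*

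**What the plan says.** All references are to the protocol article.

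- **Outcomes {12}:** success is the absence of a clinically relevant leak at 12 weeks. A relevant leak is "any leak that needs surgical revision or any other intervention, e.g., puncture or aspiration, longer hospitalization, or repeat imaging". The secondary endpoints place swelling and pseudomeningocele in a separate class that is not clinically relevant.
- **Who will be blinded? {17}:** patients are blinded. For surgical staff, "Blinding of surgical staff is not possible as L-PRF is clearly different from fibrin sealants". Three safeguards are named: ward paramedics have no access to the code, researchers are reblinded after surgery, and allocation is released only once the analysis is done.
- **Procedure for unblinding if needed {17b}:** unblinding may take place after FU3, or "in case of any serious adverse event that is probably related to the study".
- **Adverse events reporting and harms {22}:** one of the criteria for a serious event is that it "requires hospitalization or prolongation of existing hospitalization".
- **Plans for assessment and collection of outcomes {18a}:** postoperative data come from the electronic patient files. "Intraoperative data and used materials are collected from the neurosurgical report".
- **Intervention description {11a}** and **Strategies to improve adherence {11c}:** the study coordinator prepares the L-PRF and is present during the intervention.

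**The concern.** Two of the actions that turn a leak into a failure, a longer stay and repeat imaging, are matters of judgement. The boundary they police is soft: a swelling left alone is not clinically relevant, but the same swelling re-imaged or aspirated meets the primary definition. People who know the arm are in a position to influence that step.

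The unblinding rule adds a second, smaller route. A longer stay is both a failure criterion and a criterion for a serious event, so part of the primary endpoint overlaps with the events that may be unblinded early. The rule does not require the leak to be classified first and does not limit who is told. A patient who leaked could learn the arm before completing the EQ-5D and RAND SF-36 at FU3.

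In a non-inferiority trial, under-calling leaks in the experimental arm favours the claim, and with few events it takes little to matter.

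**Working it through.** **Inputs (Sample size {14}).** Control: "The assumed success rate is 93.7% in the control arm", a 6.3% leak rate. L-PRF: "we assume a 95% success rate based on a prior feasibility study", a 5% leak rate. The margin is 5 points, "using a one-sided alpha of 0.05 and 80% power", with 167 per arm (334 in total) and 350 enrolled (175 per arm).

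**Step 1. The plan's figure.** With unpooled variance,
n = (1.645 + 0.842)² × (0.937 × 0.063 + 0.95 × 0.05) / (0.05 + 0.013)² = 165.9, so 166 per arm. The stated 167 is reproduced within rounding. Power at 167 per arm is 80.2%.

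**Step 2. Expected failures.** At 167 per arm: 167 × 0.063 = 10.5 control and 167 × 0.05 = 8.4 L-PRF. At 175 per arm: 11.0 and 8.8.

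**Step 3. How many events separate success from failure.** Upper bound of the leak difference (L-PRF minus control) = d + z × √[p₁(1−p₁)/n + p₂(1−p₂)/n], holding control at 11 leaks. Non-inferiority needs a bound below 5 points.

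| n per arm | Interval | L-PRF leaks | Upper bound (points) | Non-inferior? |
|---|---|---|---|---|
| 175 | 90% | 12 | 0.57 + 1.645 × 2.649 = 4.9 | yes |
| 175 | 90% | 13 | 1.14 + 1.645 × 2.701 = 5.6 | no |
| 167 | 90% | 11 | 0 + 1.645 × 2.715 = 4.5 | yes |
| 167 | 90% | 12 | 0.60 + 1.645 × 2.771 = 5.2 | no |
| 175 | 95% | 10 | −0.57 + 1.960 × 2.539 = 4.4 | yes |
| 175 | 95% | 11 | 0 + 1.960 × 2.595 = 5.1 | no |

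The 90% interval matches the one-sided 0.05 of the sample size section. The two-sided 95% interval is the one that Statistical methods {20a} says will be reported. The tipping point moves with n and with the interval, but in each case one event separates the two conclusions.

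**Step 4. What differential calling could do (illustration).** Assume that true L-PRF success is 88.7%, exactly at the margin (11.3% leaks), and that a share f of L-PRF leaks is managed or labelled as not clinically relevant. With 167 per arm, the chance of wrongly declaring non-inferiority is:

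| f | Patients moved (167 × 0.113 × f) | One-sided 0.05 | Lower limit of 95% interval |
|---|---|---|---|
| 0 | 0 | 5.0% | 2.5% |
| 10% | 1.9 | 10.2% | 5.7% |
| 20% | 3.8 | 19.3% | 11.8% |
| 30% | 5.7 | 33.1% | 22.6% |

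In the other direction, under-calling control leaks by 10%, 20% or 30% at the planned rates lowers power from 80.2% to 74.6%, 67.9% or 60.2%. The documents give no value for f.

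**Step 5. Which endpoint leaks fall under the unblinding rule.** Set the failure criteria beside the serious-event definition:

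- Longer hospitalization: meets it directly.
- Revision: meets it where it requires or prolongs a stay.
- Outpatient puncture or aspiration, or repeat imaging alone: need not meet it.

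The overlap is therefore a subset of failures, narrowed further by the requirement of probable relatedness.

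**The case against.** A reader might infer more than the documents support.

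- **That every primary-endpoint leak is a serious event that opens the blind.** It is not. Some failures need not be serious, the rule is permissive, and it requires probable relatedness. Leakage is also a known complication of cranial surgery in general, so relatedness is not automatic.
- **That events are classified by surgeons with allocation known.** No section says who classifies a leak, or whether coding precedes or follows unblinding. The operating surgeon is not named as deciding on imaging or length of stay.
- **That unblinding drives the failure criterion.** Where the serious event is the longer stay or the revision itself, that action comes before any unblinding it permits. The surgical staff's knowledge of the arm is the stronger route.
- **That the patient is the only blinded party, or that early unblinding has no care purpose.** The blinding section names ward-staff and researcher safeguards, and clinicians outside the operating team may need the arm.

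It is also fair to say that any binary test has a one-event tipping point, which does not measure bias, and that a condensed article may leave endpoint coding to the full protocol.

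What remains is in the text: discretionary failure criteria, surgical staff who know the arm, and an early unblinding rule with no requirement to fix the endpoint first. The safeguards do not fully answer this. Reblinding cannot remove what a coordinator who prepared the L-PRF has seen, and withholding allocation until after the analysis protects the analysis, not the earlier calling of events.

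**Conclusion.** The point holds as an unguarded risk, not as a demonstrated bias. The main weakness is that part of the primary endpoint rests on decisions open to staff who know the arm. The early unblinding of some endpoint leaks is secondary.

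With about 8 to 11 failures expected per arm, one or two borderline events can change the conclusion. The exact tipping point depends on the number evaluable and the interval used: 12 against 13 L-PRF leaks at 175 per arm with a 90% interval, 11 against 12 at 167, and 10 against 11 at 175 with a 95% interval, each with 11 control leaks. The error rates in Step 4 rest on assumed misclassification shares and show a range only. For the patient-reported outcomes no size can be given; they are secondary, and only unblinded patients who leaked would be affected.

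The remedy uses data already collected, so the change is worth making.

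**What to change.** 1. **Procedure for unblinding if needed {17b}:** keep the safety provision. Add that a leak is coded against the primary definition before any non-urgent unblinding, that disclosure is limited to those who need it, and that the patient and research staff otherwise stay blinded until the FU3 questionnaires are completed.
2. **Outcomes {12} and Statistical methods {20a}:** prespecify a sensitivity analysis of the primary endpoint that counts only the hard components (surgical revision, puncture, aspiration or drainage), reported beside the full definition.
3. **Composition of the coordinating center and trial steering committee {5d}:** where feasible within the existing supervisory committee, have members who did not operate on the patient classify suspected leaks from summaries with product names removed.

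**Cost:** protocol wording, some preparation time for the summaries, and fewer events (so wider intervals) in the sensitivity analysis. Treatment and sample size do not change. Recruitment began in January 2020, so the first item cannot reach patients who have already completed follow-up. The second applies to all patients, and the third can be applied to leaks already recorded.
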